### Eligibility criteria

#### Inclusion criteria

Pregnant First Nations women with a current gestation of 28^+0^ to 34^+6^ weeks, aged 17–40 years (inclusive) residing in a participating community and intending to do so until their infant reaches 12 months of age. Eligibility includes dichorionic diamniotic (DCDA) twin pregnancies and previously enrolled mothers.

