### Assignment of interventions

#### Sequence generation

Sequential randomisation codes were computer-generated using permuted blocks (two blocks of differing sizes), stratified by community (urban and remote). The allocation ratio within these strata is 1:1 (vitamin D: placebo). There is one random allocation per mother–infant pair.

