#### Allocation implementation

Good Clinical Practice (GCP) trained research nurses or First Nations health practitioners allocate the study medicine to each mother–infant pair by selecting the next sequentially labelled (prerandomised) study medication from the appropriate stratification group. The allocation sequence number is recorded by the research team on the data collection form (DCF), the database and in the participant’s medical record. Infants receive the same allocation as their mother.

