#### Statistical analyses

The RCT is being conducted and reported according to CONSORT (Consolidated Standards of Reporting Trials) guidelines.^54^ A detailed statistical analysis plan will be developed by the investigators and study statisticians prior to the unblinding and final analysis.

The primary ‘intention-to-treat’ analysis will compare the incidence of infant ARI (episodes/child/12 months) between active and placebo groups using a negative binomial regression model and producing an estimate of the incidence rate ratio (IRR) with 95%CIs. The model will include terms to account for repeat mothers and twins. There will be no imputation for missing data. Supplementation efficacy will be defined as (1−IRR)×100.

Secondary analyses (clinical) will include between group comparisons of (1) the proportion of children having any ARI episode <12 months (using a generalised linear model with effects presented as risk ratios), (2) time to first ARI presentation (using Cox regression with effects presented as HRs) and (3) the incidence of ARI subgroup outcomes (pneumonia, bronchiolitis and OM using negative binomial regression with effects presented as IRRs). Sensitivity analyses will include those (1) with hospitalised outcomes and (2) clinical outcomes requiring antibiotics. A per-protocol analysis (excluding those who missed >3 consecutive doses) will also be conducted for all clinical outcomes.

Secondary analyses (biological) will compare between-group differences in (1) circulating vitamin D levels: mean plasma 25OHD at each visit and breast milk 25OHD at birth (Student’s t-test), (2) microbiological outcomes: proportions of nasal swabs positive for *S. pneumoniae*, NTHi and RSV using χ^2^ tests and reporting risk ratios with 95% CIs and (3) immune function measures: median immune cell population counts in cord blood at birth and infant blood at 4 months; median circulating inflammatory marker levels in cord blood at birth and infant blood at 4 months; median CBMC population counts and CBMC challenge-induced cytokine levels (Wilcoxon rank-sum test); geometric mean concentrations of IgG and IgA to pertussis vaccine antigens in maternal plasma and breast milk; geometric mean concentrations of IgG and IgA PCV serotype antigens (five types) in infant saliva and plasma at age 4 months (Student’s t-test). All data will be analysed using Stata Statistical Software: Release V.17 (StataCorp) and GraphPad Prism V.9 (GraphPad Software, USA).

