Of note, recent evidence suggests daily dosing is most effective clinically.^31^ Further, there is emerging biological evidence to suggest bolus dosing is ineffective due to upregulation of 24-hydroxylase (converts 25OHD and 1,25OH_2_D_3_ into less active 24-hydroxylated products) and FGF23 (inhibits 1α-hydroxylase which is necessary to locally convert circulating 25OHD into active 1,25OH_2_D_3_) that act to balance the vitamin D response.^56^ However, these studies^57 58^ compare large bolus doses >150 000 IU with daily doses and the biological effect of moderate weekly doses (<14 000) remains unclear. One meta-analysis suggests that daily dose equivalents of 2000 IU or less in individuals with circulating 25OHD<100 nmol/L are unlikely to induce the same down regulation in vitamin D function as large bolus doses.^59^ Our study will contribute valuable data on the clinical and immunological effects of weekly vitamin D dosing in infants.

There are also many challenges. The trial is being conducted throughout a pandemic. While the D-Kids trial has never officially paused, lockdowns, isolation and quarantine measures designed to reduce the spread of SARS-CoV-2 have restricted face to face contact, interaction with medical facilities and general travel, impacting participant recruitment and follow-up, and reducing the rates of ARI. As of December 2022, 184 infants had been recruited to the study. Several strategies have been implemented to mitigate slow recruitment including the addition of new study sites (notably Alice Springs in Central Australia), self-administered dosing, clinic assisted follow-up visits, and recruitment of twins and previously enrolled mothers. Notably, while self-administered dosing mimics the real-world setting, adherence (phone-based reporting) becomes more difficult to accurately monitor. With pandemic measures easing in 2023, we are optimistic about achieving our recruitment target.

Feasible interventions such as vitamin D supplementation show considerable potential against ARI but more evidence is required. Our study outcomes will make an important contribution to clinical practice, the medical literature and could have profound implications for disadvantaged populations where ARIs are common.

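### The two-sample tests fixed for infant biological outcomes ignore the twin pairing that the primary model allows for, so their standard errors are slightly too small (minor)

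*Protocol article*

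**What the plan says.** All references are to the protocol article.

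- **Who can enter (Inclusion criteria):** "Eligibility includes dichorionic diamniotic (DCDA) twin pregnancies and previously enrolled mothers". The Discussion lists "recruitment of twins and previously enrolled mothers" among the measures taken against slow recruitment. Neither place gives a number.
- **How siblings are allocated:** Allocation implementation states "Infants receive the same allocation as their mother", so twins are always in the same arm. Sequence generation states "There is one random allocation per mother–infant pair", which suggests that a later pregnancy of the same mother gets a new allocation.
- **Primary analysis (Statistical analyses):** "The model will include terms to account for repeat mothers and twins". This stands in the paragraph on the primary negative binomial model and is not repeated.
- **Biological analyses (same section):** for vitamin D, "mean plasma 25OHD at each visit and breast milk 25OHD at birth (Student’s t-test"; for nasal pathogens, chi-square "tests and reporting risk ratios with 95% CIs"; for immune measures, a list ending in "CBMC challenge-induced cytokine levels (Wilcoxon rank-sum test". Geometric mean antibody concentrations are compared by Student's t-test. None of these carries an allowance for siblings.
- **Error control:** each analysis is judged at p below 0.05 with no multiplicity adjustment. A detailed SAP is to be written before unblinding.

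**The concern.** Twins share a mother, her vitamin D status, her supplementation and her arm. Cord 25OHD, early-infancy 25OHD, nasal carriage and antibody levels are plausibly alike within a pair. Two same-arm infants who resemble each other carry less information than two unrelated infants, and an ordinary two-sample test counts them as two full observations. Its standard error is then too small, in a known direction.

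The plan recognises this dependence for the primary outcome and then fixes tests that cannot accommodate it for outcomes tied to its stated secondary aims (vitamin D status, nasal pathogens, immune response). With no multiplicity adjustment, the nominal level of each single test is the only error control these outcomes have. The share of siblings is also not settled: 184 of 314 infants had been recruited by December 2022, so 130 (41%) were still to come with twins and previously enrolled mothers eligible.

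**Working it through.** **1. The plan's own figure.** The only related figure is the primary sample size. With rates 3.50 and 2.54 per year, k = 0.4, two-sided 5% (sidedness assumed) and 90% power:

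n per arm = (1.960 + 1.282)² × (1/3.50 + 1/2.54 + 2 × 0.4) / [ln(2.54/3.50)]² = 151.2

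That is 152 per arm and 304 in total; 304/0.97 = 313.4 after 3% loss, against the stated 314. It reproduces. It assumes independent infants and does not bear on the biological tests, for which the plan states no figure.

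**2. Same-arm twins.** Inputs: t, the share of infants who are twins, and ρ, the within-pair correlation within arm. Neither is in the documents, so both are assumptions. For n infants in an arm, of whom 2m form m twin pairs, the variance of the mean is (σ²/n)(1 + 2mρ/n). So:

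- design effect DE = 1 + tρ
- true SE / naive SE = √DE
- shortfall of the naive SE = 1 − 1/√DE
- true level of a nominal 5% test = 2[1 − Φ(1.96/√DE)]

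| t | ρ | DE | True/naive SE | Naive SE too small by | True level |
|---|---|---|---|---|---|
| 2% | 0.3 | 1.006 | 1.003 | 0.3% | 5.1% |
| 2% | 0.8 | 1.016 | 1.008 | 0.8% | 5.2% |
| 5% | 0.3 | 1.015 | 1.0075 | 0.7% | 5.2% |
| 5% | 0.8 | 1.040 | 1.020 | 1.9% | 5.5% |
| 10% (extreme) | 0.8 | 1.080 | 1.039 | 3.8% | 5.9% |

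In a trial of 314, these shares are about 3, 8 and 16 twin pairs.

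**3. Simulation of the three named tests.** Settings: N = 314, no treatment effect, 20,000 replicates per scenario, ρ = 0.5 and 0.8 on an underlying normal scale, binary outcome cut at the median. Monte Carlo standard error is √(0.05 × 0.95/20,000) = 0.15 percentage points. With no siblings, the three tests gave 4.7% to 5.1%.

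| Scenario | t-test | Chi-square | Wilcoxon |
|---|---|---|---|
| 8 twin pairs | 5.3–5.5% | 4.8–5.0% | 5.1–5.4% |
| 16 twin pairs | 5.8% | 5.3–5.4% | 5.7% |
| 8 or 16 repeat-mother pairs, newly randomised | 4.8–5.2% | 4.8–5.0% | 4.9–5.1% |
| 5 twin pairs + 8 repeat pairs kept in one arm | 5.3–5.8% | 5.0–5.5% | 5.2–5.8% |

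The twin results agree with the formula. The effect is weaker for the binary outcome because cutting a scale in two lowers the within-pair correlation. For newly randomised repeat mothers, same-arm pairs make the naive SE too small and opposite-arm pairs make it too large; on average these cancel.

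**4. Which outcomes are exposed.** Maternal 25OHD, breast-milk 25OHD and antibodies in maternal plasma or breast milk are measured on the mother, so twins add no second observation. Cord and infant 25OHD, nasal swabs, infant antibodies, and cord or infant immune measures can contribute two values per twin pair. Pertussis antibody joins this group if cord plasma is used, as Tertiary outcomes has it; Statistical analyses names maternal plasma.

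**The case against.** The strongest reply is that this is detail for the SAP, and that the effect is negligible. Monochorionic diamniotic twins are excluded and dichorionic twins need obstetrician approval, so twins should be few, and no secondary conclusion is shown to be at risk. The immunological outcomes are described as explanatory and are to be presented separately.

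The size argument stands and sets the severity. The SAP argument stands only in part. For the biological outcomes the article is not silent: it names tests that conflict with a dependence it acknowledges in the same section. A SAP that follows those tests inherits the problem.

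A reader might infer more than the documents support:

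- **That the secondary clinical models share the fault.** The generalised linear, Cox and subgroup models state no sibling term, but they can carry clustered standard errors. Silence there is properly left to the SAP.
- **That the primary model is deficient** because its terms could be mere twin or repeat-mother indicators. The wording equally fits a mother-level random effect, so this is a supposition.
- **That repeat mothers distort the tests.** With a new allocation at each pregnancy they do not do so systematically.
- **That the error is large.** Even 15% of infants in same-arm pairs with correlation 0.9 gives √1.135 = 1.065, a naive SE 6.1% too small, and nothing in the documents supports such a share.

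**Conclusion.** The point holds in a narrow form and is minor. For infant-level and cord-level biological outcomes, the named t, chi-square and rank-sum tests treat twins as independent although they share a mother and an arm. Standard errors, where the test yields one, and p values are slightly too small: about 0.3% to 2% in the standard error, with a true level of 5.1% to 5.5%, if 2% to 5% of infants are twins with correlation 0.3 to 0.8. Those inputs are assumptions, because the documents give neither.

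It would be too strong to call the intervals for these outcomes wrong in any way that could change a conclusion, or to extend the point to the primary analysis. The finding on repeat mothers rests on reading Sequence generation as a new allocation per pregnancy. If mothers instead kept their arm, the level with 5 twin and 8 repeat pairs at correlation 0.8 would be about 5.5% to 5.8%.

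**What to change.** State in the SAP, before unblinding:

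- **Infant and cord 25OHD, infant antibody concentrations:** linear regression on arm (raw scale for 25OHD, log scale for antibodies), with standard errors clustered on mother across enrolments. The mean difference and the ratio of geometric means are unchanged as estimands.
- **Nasal pathogens:** modified Poisson regression for the risk ratio, with the same clustered standard errors. The estimand is again unchanged.
- **Rank-based immune outcomes:** keep the comparison of medians or ranks. Linear regression would replace it by a comparison of means, which is a different question for skewed data. Add a rank test that allows for clustering, or a sensitivity analysis with one infant per mother chosen by a rule fixed before unblinding.
- **Reporting:** give the number of twin pairs and repeat mothers by arm, and say whether a repeat pregnancy received a new allocation.

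The cost is a few sentences in the SAP, routine options in the named software for the regressions, and intervals wider by about 0.3% to 2% under the assumptions above. The one-infant-per-mother analysis drops a few observations, which is acceptable for a sensitivity analysis.

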### Monitoring

#### Data monitoring and harm assessment

An iDSMC was established prior to any participant recruitment. The committee includes experienced study independent statisticians, clinicians, endocrinologists and epidemiologists. SAEs (hospital admissions) and other AEs are monitored by study staff through hospital visits, participant contact and regular review of participant medical records. Each SAE is reported to an independent medical monitor (an experienced paediatrician not on the iDSMC) to review causality. SAEs deemed as potentially related to the study are reported to the iDSMC and Human Research Ethics Committee (HREC) within 72 hours. At regular intervals (<6 months), the iDSMC assess the totality of information relating to participant recruitment and retention, protocol deviations and violations, AEs and SAEs. Unblinding can be requested where concerns arise. With compelling evidence, the iDSMC can recommend cessation of the trial. Given vitamin D is low risk, there are no predefined stopping rules or planned interim analyses. A First Nations Reference Group oversees cultural aspects of the study.

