## Introduction

### Background and rationale

Acute respiratory infections (ARIs) remain the greatest global cause of childhood morbidity and mortality.^1^ The largest burden occurs among socioeconomically disadvantaged populations.^1^ In Australia, First Nations children are hospitalised with ARIs up to nine times more often than other children.^2^ The gap is widest in the Northern Territory (NT) where, despite government funded healthcare, high vaccine coverage and almost universal early breast feeding,^3 4^ rates of early-onset pneumonia (20% hospitalised in first year),^4^ otitis media (OM) (90% at age 6 months)^5^ and chronic suppurative lung disease (1 in 68 in Central Australia)^6 7^ are among the highest reported in the world. Further, the burden of ARI hospitalisation in the NT has changed little over the last two decades.^3 8^ Slow progress in improving health services and addressing the social determinants of health drives the need for novel, effective, community endorsed, evidence-based interventions to reduce the burden of ARIs in the region. Oral supplementation of vitamin D, integral to immune function,^9 10^ is one such intervention that could reduce infants’ susceptibility to ARIs.^11 12^

Vitamin D is a steroid-like molecule generated predominantly on exposure of skin to sunlight with the remainder coming from the diet.^13^ Cutaneously generated (vitamin D_3_) or ingested vitamin D (vitamin D_2_ or D_3_) is hydroxylated by the liver into 25-hydroxy-vitamin D (25OHD) which is considered the best measure of vitamin D status. The active hormonal form of vitamin D, 1,25 hydroxy-vitamin D3 (1,25OH_2_D_3_) is produced by the kidney or locally by specialised cells of other systems as required. Both 25OHD and 1,25OH_2_D_3_ are transported in the circulation by the vitamin D binding protein.^14^ Active vitamin D regulates gene expression via the vitamin D receptor (VDR).^15^ Conventionally, vitamin D is known for its role in regulating calcium metabolism though the effects of vitamin D and its metabolites are much broader.^16^

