## Methods

### Trial design and setting

‘D-Kids’ is a parallel (1:1), double-blind, allocation concealed, randomised, placebo-RCT of weekly perinatal vitamin D supplementation (figure 1). The trial is being conducted among First Nations families in urban and remote communities of Australia’s NT. The NT is sparsely populated with approximately 229 000 residents spread across 1.4 million km² (0.16 people per km²).^32^ Approximately 70% of NT First Nations families reside in remote communities.^32^ Recruitment started in February 2019 and the study is scheduled for completion by the end of 2024.

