Visit 1, enrolment: Pregnant mothers are eligible for enrolment at 28^+0^ to 34^+6^ weeks gestation. At this visit, we provide a detailed explanation of the study rationale and requirements using plain language study material (including a participant information sheet, pictorial flipchart and consent form). First Nations team members translate materials as necessary. Interested families are formally invited to participate in the study. With written informed consent and confirmation of eligibility, mothers are enrolled and randomly allocated to the intervention or placebo arm. A baseline blood sample is collected prior to supervised administration of the first dose of study medicine.

Visit 2, birth: At delivery, cord blood is collected by the attending obstetricians or midwives and transported to the laboratory for processing within 24 hours. Study staff visit mothers and their babies within 14 days of birth. The visit coincides with the end of the maternal supplementation. Blood and breast milk (at least 3 days post partum) are collected from mothers. Blood and saliva are collected from neonates. Infant study medicine is commenced, and the first dose is administered.

Visit 3, infant age 4 months: Families are visited when infants are 3.5–6 months of age, coinciding with the end of the infant supplementation period (16th week post partum). An infant blood, nasal swab and saliva sample are collected.

Visit 4, infant age 12 months: The final study visit occurs between infant ages 11–18 months. An infant blood and nasal swab are collected. Families receive a small thankyou gift for their contribution.

Routine data are collected at each visit, including personal, household and community demographics, medical and vaccination history, smoke exposure, time spent indoors and use of vitamin D or other supplements, breastfeeding status and infant growth metrics. Serious adverse events (SAEs) and clinical outcomes are monitored via maternal and infant medical records (hospital and primary care) throughout follow-up.

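### The article equates a serious adverse event with a hospital admission, so a death or other grave event without admission falls outside causality review and the 72-hour report

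*Protocol article*

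**What the plan says.** The harm text is in the Protocol article, section Data monitoring and harm assessment. It says that "SAEs (hospital admissions) and other AEs are monitored by study staff through hospital visits", and also by contact with participants and review of their records. It then sets out three levels of review.

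- Causality: "Each SAE is reported to an independent medical monitor (an experienced paediatrician not on the iDSMC) to review causality".
- Expedited report: "SAEs deemed as potentially related to the study are reported to the iDSMC and Human Research Ethics Committee (HREC) within 72 hours".
- Periodic review: "At regular intervals (<6 months), the iDSMC assess the totality of information relating to participant recruitment and retention, protocol deviations and violations, AEs and SAEs".

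The first two levels name SAEs only. The third covers all adverse events.

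Section Study visits adds where SAEs are found: "Serious adverse events (SAEs) and clinical outcomes are monitored via maternal and infant medical records (hospital and primary care) throughout follow-up".

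No other criterion of seriousness appears in the article. Its harm text does not mention participant death, stillbirth, life-threatening events or disability. Congenital anomaly appears once, under Additional criteria, where it triggers paediatrician approval for the infant to stay in the study. That sentence is not linked to adverse event reporting.

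**The concern.** An article may leave the full list of seriousness criteria to the full protocol, and that alone would be no fault. Here the article does supply a meaning for SAE, and the meaning is too narrow. Because the bracket is set against other AEs, the sentence works as a partition: an event with a hospital admission is serious, and any other event is not. The test is where care was given, not how grave the outcome was.

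The trial doses women in late pregnancy and infants from birth to 4 months, and Trial design and setting states: "Approximately 70% of NT First Nations families reside in remote communities". A grave event away from hospital is therefore plausible. Such an event most needs a prompt, individual judgement on whether study medicine could be involved. As worded, the plan gives it neither the individual judgement nor the short reporting deadline. The article also says there are no predefined stopping rules and no planned interim analyses, so the SAE route is the only expedited reporting deadline it describes.

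**Working it through.** There is no stated figure to reproduce. The check is to apply the sentence as written to each kind of event.

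**Inputs**
1. SAE means a hospital admission (Data monitoring and harm assessment).
2. The medical monitor's causality review covers each SAE (same section).
3. The 72-hour report to the iDSMC and the ethics committee covers SAEs judged potentially related (same section).
4. The periodic iDSMC review covers AEs and SAEs, at intervals under 6 months (same section).
5. Infant dosing runs from birth to 4 months (Intervention).

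**Literal application**

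| Event | Admission? | Causality review | 72-hour report | Periodic review |
|---|---|---|---|---|
| Infant or maternal death in the community | No | No | No | Yes |
| Life-threatening event managed at a remote clinic | No | No | No | Yes |
| Congenital anomaly first found outside an admission | No | No | No | Yes |
| Stillbirth delivered in hospital | Yes | Yes | If judged potentially related | Yes |
| Anomaly seen during the hospital birth stay | Yes | Yes | If judged potentially related | Yes |
| Infant admitted with a respiratory infection | Yes | Yes | If judged potentially related | Yes |

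The gap is the first three rows: grave events with no admission.

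**What the gap means in time.** The expedited route allows 72 / 24 = 3 days. Without it, an event waits for the next periodic review, which could be anything up to just under 6 months away. That maximum is longer than the 4 months of infant dosing, so an event in one infant might not be considered by the iDSMC until other infants on treatment at that time had finished.

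**Does the section on Study visits close the gap?** It says SAEs are sought in hospital and primary care records. That fixes the source of detection. It does not say which events found there are serious. A death noted in a clinic record would be found, but the harm section would still class it as an other AE. The passage is compatible with a wider definition but does not state one.

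**Routine delivery.** Study visits describes births attended by obstetricians or midwives, and no admission is exempted from the bracket. Whether a normal hospital birth counts is therefore left to inference. If it did count, it would enter the causality step. It would reach the 72-hour step only if judged potentially related.

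**How many events.** The article gives no rate for deaths, out-of-hospital life-threatening events or late-found anomalies, so no count can be derived. The 70% figure describes families in the Northern Territory, not enrolled pairs. It supports plausibility, not a number.

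**The case against.** The strongest objection is that two bracketed words in a condensed article are being read as the trial's whole definition. The Registration section cites a full protocol, version 2.1, which is not shown and may well list wider criteria, with the bracket as shorthand or the main example. Looking for SAEs in primary care records fits that. This stands as a real possibility. It limits the severity and is why the remedy includes alignment with the full document. It does not remove the point, because the published sentence is what a reader has, and it draws the line in the wrong place.

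A second objection is that these events are not lost. Other AEs are monitored through participant contact and record review, the iDSMC sees them periodically, and the Blinding section allows unblinding on evidence of a safety concern without limiting this to SAEs. That is correct. What is missing is the individual causality assessment and the short deadline, not all oversight.

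Three stronger readings are tempting, and the document does not support them.

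- *Stillbirths and anomalies in general are missed.* Those delivered or seen during a hospital birth stay involve an admission and so fall inside the literal rule. Only events without an admission fall outside.
- *Routine births swamp the SAE count.* One might set about 314 deliveries (one per pair, assuming hospital birth) against 0.20 x 314 = 62.8, about 63 infants, from the Background figure: "rates of early-onset pneumonia (20% hospitalised in first year". The comparison fails. Counting births at all rests only on the lack of a printed exemption, and an uncomplicated delivery is arguably not an adverse event. The 63 covers pneumonia only and leaves out all other infant admissions and all maternal admissions.
- *A comparison of SAEs by arm would be diluted.* The article plans no such comparison.

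**Conclusion.** The point holds in a narrow form. As written, a death, life-threatening event or congenital anomaly that occurs or is found without hospital admission gets no individual causality review and no 72-hour report. It reaches the iDSMC only at a periodic review that may be almost 6 months away.

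This is a fault in a stated rule rather than a missing detail. Severity is modest. The affected events are presumably few, their number cannot be derived from the document, periodic oversight remains, and no sample size, power or analysis figure changes. It is still worth correcting, because it concerns prompt review of the gravest outcomes.

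The conclusion rests on two assumptions: that staff would apply the bracket literally, and that the full protocol does not already define SAEs more widely. If the second is false, what remains is a discrepancy between the article and the protocol. The delivery question is a clarification only.

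**What to change.** Replace the bracket with outcome-based seriousness criteria for mother, fetus and infant: death (including stillbirth), life-threatening event, persistent disability and congenital anomaly, as well as hospitalisation. If protocol version 2.1 already has a wider definition, align the sentence with it instead. State that every event meeting these criteria goes to the existing medical monitor and, if potentially related, through the existing 72-hour report, wherever the event took place. As a clarification, add that admission for uncomplicated delivery is not in itself an SAE.

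The cost is a short amendment, which under Protocol amendments needs ethics committee review and approval, and an updated SAE form. No new visits or tests are needed, since hospital and primary care records are already reviewed. Events already recorded as other AEs could be checked once against the revised criteria.
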